### Control practices

The control practices are only contacted at the time of randomisation and their contribution to the study (collection of data in 12 months’ time) is explained to them at the set-up telephone conversation shortly after they have been randomised. The study team do not contact the control practices again until at the end of the intervention period; control practices will be asked to install and run a ‘dummy version’ of the audit using the Audit + software to search for high-risk HCV patients retrospectively (i.e. the same calendar period as for the intervention practices). These data will be used to compare control and intervention practices to assess the impact of the intervention at the individual patient level as well as at the practice level. At the end of the study period, the control practices will be provided with the software licence for approximately 1 year and can choose to use any of its applications including the HCV audit.

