The practice manager will be asked to install the Audit + software onto the practices’ clinical system. Practice staff training will include details on how to install and use the Audit + software as part of the intervention. Within the Audit + software, the HCV audit will be used to identify potentially eligible patients who have pre-defined Read codes defining them as ‘high-risk’ (see Appendix). The Audit + software identifies all patients with one or more of the codes. Patients excluded are those: tested recently for HCV; who have been referred to hepatology; receiving palliative care; who have raised ALT and tested for HCV. The audit will be run and updated every 24 hours on the GP system. GPs will be asked to screen the resultant list at the beginning of the intervention and then regularly, at intervals defined by the practice, to identify new patients during the remainder of the study period. GPs will be permitted to exclude any patient identified by the audit where they feel that an invitation for HCV testing or discussion of treatment is not appropriate. Eligible patients’ records identified by the audit will be automatically flagged by the software to encourage opportunistic testing if the patient attends the surgery. Practice staff can manually switch off the flagging should they feel that the patient is not eligible for a HCV test, if the patient declines a test or if the patient accepts the offer of a test, by entering a specific set of Read codes. Practice staff administrators will also be asked to send out a letter to each patient identified by the audit informing them that the practice is taking part in a study and that they may contact patients by telephone, e-mail or text (whichever is preferred by the practice) to book an appointment to discuss having a test. The patient invitation letters will be automatically processed using the integrated mail-merge facilities built within the software. Diagnosed patients are managed as usual/in standard care at the practice.

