#### Primary outcome measures

*The number and proportion of high-risk patients tested for HCV*. The total number of HCV tests performed at the intervention practices and at the control practices during the intervention period will be collected by PHE laboratories

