## Appendix

### HCV audit

A HCV test algorithm was developed and piloted at two local general practices before its integration into the Audit + software (BMJ Informatica). The HCV test algorithm was designed to identify registered patients with high-risk HCV markers or patients previously diagnosed who failed to initiate or complete treatment. The search terms included (1) age 18–75 years old, (2) previous intravenous drug use (IDU) history, (3) opiate prescription (including methadone or buprenorphine), (4) opiate misuse, (5) blood transfusion prior to 1991, (6) blood products prior to 1996, (7) transplant prior to 1992, (8) infection with HIV, (9) infection with hepatitis B virus (HBV), (10) born to a mother with HCV, (11) child in care, (12) prison history, (13) altered ALT levels, (14) patients tested for HCV over 1 year previous, before the intervention. Identified individuals considered by GPs to be unsuitable for a discussion about HCV testing or treatment were excluded. Patients also automatically excluded by the HCV audit included (1) patients referred to hepatology, (2) patients tested less than 1 year prior to the intervention, (3) patients receiving end of life/palliative care, and patients with raised ALT levels who have been tested for HCV.

The list of codes are available from the authors and given in Additional file 1. Spirit Checklist also available in Additional file 2.

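### The high-risk list that forms the denominator is built live in one arm and retrospectively in the other, and two exclusions that overlap with outcomes are not tied to the start of the intervention

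*Protocol article*

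**What the plan says.** The primary outcome (Protocol article, Primary outcome measures) is "The number and proportion of high-risk patients tested for HCV". The secondary outcomes (antibody and RNA positivity, referral, first assessment, treatment start) are also numbers and proportions of high-risk patients. High-risk means picked out by the audit, so the audit list is the denominator of all these proportions.

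**Intervention practices** (Identification of patients with risk markers of HCV or patients previously diagnosed): "The audit will be run and updated every 24 hours on the GP system". GPs screen the list at the beginning and at intervals after that.

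**Control practices** (Control practices): the team makes no contact between set-up and the end of the intervention period. The practice then installs a dummy version of the audit "to search for high-risk HCV patients retrospectively (i.e. the same calendar period as for the intervention practices".

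**Exclusions.** The Methods text removes recently tested patients and those "who have been referred to hepatology; receiving palliative care; who have raised ALT and tested for HCV". The Appendix (HCV audit) repeats the list. It dates one item to before the intervention, "patients tested less than 1 year prior to the intervention". It leaves hepatology referral and "patients with raised ALT levels who have been tested for HCV" undated.

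**The concern.** Being tested is the primary outcome and being referred is a secondary outcome. Each also appears in an exclusion rule, the test in combination with raised ALT. Altered ALT is in addition one of the search terms, so for a patient who enters the list on ALT, having the primary outcome meets an exclusion.

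In the intervention arm a patient can be listed before any test or referral takes place. In the control arm the list does not exist until the year is over, when the record already holds that year's tests and referrals. An undated exclusion applied to that record would select on the outcome, and it would remove events from the control numerator and denominator together. The bias would run towards the intervention. It would be most severe for referral and the steps that follow it.

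The problem is hard to repair later. Individual data are collected for patients whom the audit identifies, and they are anonymised before they reach the research team (Outcome measures and statistical analysis). A control patient dropped by the query cannot afterwards be recognised as high-risk.

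**Working it through.** **1. The plan's own figures.** From Sample size: 5% versus 17%, 90% power, 5% significance (two-sided assumed), ICC 0.05, 10 patients per practice.
- Design effect = 1 + (10 − 1) × 0.05 = 1.45.
- Two proportions with continuity correction: 158 per arm. 158 × 1.45 = 229.1, hence 23 practices per arm and 46 in total, as stated.
- With 80 patients per practice: 23 × 80 = 1840 per arm, design effect 1 + 79 × 0.05 = 4.95, effective size 1840 / 4.95 = 371.7 per arm. The stated 72% power for 1.3% versus 4.4% reproduces (72.0%).

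The sample size is sound and is not affected by this point.

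**2. The rules side by side.**

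| Exclusion | Date given | Overlaps with an outcome |
|---|---|---|
| Recent HCV test | Under 1 year before the intervention (Appendix) | No: a test during the study does not trigger it |
| Referred to hepatology | None | Yes: secondary outcome |
| Raised ALT and tested for HCV | None | Yes: contains the primary outcome |
| Palliative care | None | No |

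**3. Illustration of size.** Let f be the share of tested control patients removed by an end-dated exclusion. The article does not give f, so it is assumed over a range. Removing a tested patient takes one from numerator and denominator, so for true uptake p:

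observed control uptake = p(1 − f) / (1 − pf)

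Take p = 0.05 in both arms (no true effect) and deletion in the control arm only.

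| f | Observed control uptake | Apparent rate ratio | Type I error, 1840 per arm | Type I error, 230 per arm |
|---|---|---|---|---|
| 0 | 5.0% | 1.00 | 5% | 5% |
| 0.2 | 0.040 / 0.990 = 4.0% | 1.24 | 10% | 7% |
| 0.4 | 0.030 / 0.980 = 3.1% | 1.63 | 27% | 14% |
| 0.6 | 0.020 / 0.970 = 2.1% | 2.4 | 58% | 29% |

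The error rates use a normal approximation for two proportions with n divided by the design effect (4.95 or 1.45). For f = 0.4 and 1840 per arm: the spurious difference is 0.05 − 0.0306 = 0.0194, the pooled standard error is 0.0144, and (0.0194 − 1.96 × 0.0144) / 0.0144 = −0.62, a rejection probability of about 27%.

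At the planned rates, f = 0.2 would turn the true ratio 0.17 / 0.05 = 3.40 into 0.17 / 0.0404 = 4.21.

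**4. Referral.** If the hepatology exclusion is fully end-dated, f = 1 for this outcome: each control patient referred during the year is removed and the control count is zero.

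**5. If both arms lose such patients alike.** With true rates of 5% and 17%:
- f = 0.2: 14.1% versus 4.0%, rate ratio 3.48, difference 10.0 points.
- f = 0.5: 9.3% versus 2.6%, rate ratio 3.62, difference 6.7 points.

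Against 3.40 and 12.0 points without deletion, the ratio is roughly preserved and the risk difference, which the plan also estimates, shrinks. Ratio inflation of the size in step 3 therefore needs the exclusions to act differently in the two arms.

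**The case against.** A reader might infer that control events will be deleted and the effect inflated. The article does not support that.

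- A retrospective search over the same calendar period can be read as back-dated to its start. The exclusion nearest to the primary outcome is dated that way, and end-dating the referral exclusion would defeat a comparison that the protocol itself plans. That makes it an unlikely intention.
- Deletion in one arm only also requires intervention patients to stay in the analysis set after a test or referral. No retention rule is stated.
- For the primary outcome only tested patients who also have raised ALT, or who were referred, are at risk. The article does not give that fraction, so the error rates above are conditional on an assumed input.
- Laboratory test totals per practice do not depend on the list and offer a partial check.
- This is a condensed article, and date logic might sit in the full protocol or the code list.

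Most of this stands, and it limits the claim to a possibility. It does not remove the point. Naming the period searched does not say at what date an exclusion is judged. The Appendix dates one exclusion and leaves its neighbours in the same sentence undated. The laboratory totals do not show who was high-risk. The difference between arms in how the list is made is also a design choice that the article states, so it is more than an omitted detail.

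**Conclusion.** The concern holds in conditional form. The plan builds the denominator of its primary and secondary proportions differently by arm. It also leaves open whether two outcome-related exclusions are judged before or after the outcomes occur. If they are judged on the end-of-study record, and intervention patients stay listed, the bias favours the intervention.

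Its size is not derivable from the article. Under no true effect, 5% uptake, 1840 per arm and a design effect of 4.95, losing 20% to 60% of tested control patients would give a spurious rate ratio of about 1.24 to 2.4 and a type I error of about 10% to 58%. These figures are a range under assumptions and should not be read as an expected result. If the exclusions are in fact evaluated at the start in both arms, f = 0 and this bias does not arise. It should be settled before the dummy audit is run, because patients left out of the control extract cannot be recovered.

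**What to change.** Define the analysis set separately from the list used to deliver the intervention:

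1. Run one identical query in all 46 practices. Evaluate each search term and each exclusion at a common index date, the start of the intervention period, using only codes dated on or before it.
2. Keep everyone registered at that date, including those who later leave or die, and count laboratory and hepatology outcomes after it.
3. Use the live 24-hour list for delivery and process reporting only.
4. Do not remove patients from the analysis set through the discretion described in "GPs will be permitted to exclude any patient identified by the audit where they feel that an invitation for HCV testing", since the article describes it only for the intervention workflow.

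**Cost.** One extra query run in intervention practices, where the software is already installed, and re-dating of the existing query. Patients who first become high-risk during the year leave the primary analysis. That narrows the population, because the intervention is meant to reach them too. They can be reported in a secondary analysis under one entry rule applied identically in both arms. The number of practices does not change. Practices were still being recruited when the article was submitted, so the change could be made before any control extraction.

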### Outcome measures and statistical analysis

Data will be collected from three separate sources: general practices (using the Audit + software in the intervention practices and control practices), PHE laboratories Bristol and specialist secondary care hepatology services. During the study period we will also collect data on individuals who, from the practice electronic patient record (age, sex, postcode district, HCV risk factors as included in the algorithm) are identified by the audit as high-risk. As patient consent is not obtained, only anonymous data will be provided for the University of Bristol research team. Therefore, data will be sent by staff at the general practices and secondary care services to a data analyst at PHE laboratories. The data will then be linked using NHS numbers, GP code, name and date of birth, and anonymised and assigned a unique study ID number before sending the data to the research team at the University of Bristol.

#### Primary outcome measures

*The number and proportion of high-risk patients tested for HCV*. The total number of HCV tests performed at the intervention practices and at the control practices during the intervention period will be collected by PHE laboratories

#### Secondary outcome measures

The HCV risk factors associated with each patient identified by the audit will be recorded by the Audit + software at participating practices. We will assess:*Number and proportion of high-risk patients testing HCV antibody positive and HCV RNA positive*. The results of each screening HCV test at each of the participating practices will be collected by PHE laboratories. Follow-up tests including polymerase chain reaction (PCR) (which diagnoses chronic HCV) and viral load results will also be collected by PHE laboratories*Number and proportion of high-risk patients referred for specialist assessment*. This will be recorded by data held by PHE laboratories for each of the participating practices*Number and proportion of high-risk patients attending their initial assessment* (*and fibroscan conducted*). This will be obtained from the secondary care hepatology records at University Hospitals Bristol and North Bristol Trusts and sent to PHE laboratories for linkage*Number and proportion of high-risk patients initiating treatment*. These data will be recorded by the secondary care hepatology records at University Hospitals Bristol and North Bristol Trusts and sent to PHE laboratories for linkage

The proportion of high-risk people tested for HCV, compared between intervention and control arms as a rate ratio, will be estimated in a negative binomial regression model, adjusted for whether an individual’s practice is in Bristol or not, and whether that practice has at baseline a high HCV testing rate or not. This regression model accommodates variation in the outcome measure between GP practices. This approach will be adapted to the secondary outcome measures, and also to estimate the risk difference between intervention and control arms for the primary outcome measure. These analyses will follow the intention-to-treat principle, with practices being analysed in the arms to which they are randomised.

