**Fig. 1 Fig1:**
[figure not shown]
Trial schema and flow diagram

GP practices will be the unit of allocation. Practices will be randomised by an independent statistician in a 1:1 ratio to receive either the intervention or continue care as usual (control group). Randomisation will be stratified by area (Bristol, non-Bristol) and current rate of HCV testing (high: ≥1 % of the practice list versus low: <1 %), and minimised by practice size. In 93 practices in our target area, 15 (16 %) had HCV high testing rates.

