### Sample size

We based our initial sample size calculation on an average practice of 6500; with 4225 adults aged 15–65, we would expect approximately 1 % (42) of people to have an injecting history and in Bristol approximately 40 % (17) of those to have chronic HCV [13]. As a minimum we assume that 10 high-risk patients, based on the algorithm and markers of previous injecting history, will be identified and that the intervention increases uptake of HCV testing from 5 to 17 % of those high-risk patients. Then we require a sample size of 46 practices (23 intervention and 23 control, 230 high-risk patients identified in each arm) to achieve 90 % power at the 5 % significance level. We have assumed an intra-cluster correlation coefficient (ICC) of 0.05, and hence a design effect of 1.45, to accommodate variation in testing rates across practices.

This is a conservative sample size calculation to ensure a large enough number of practices and sufficient power to measure the main intervention effect on uptake of HCV case-finding and diagnosis as well as referral and assessment for treatment. First, practices being approached for the study and identified by the CRN have an average practice list size of 10,000 and, therefore, approximately 6500 adults aged 15–65. Second, it is likely that 2 % of adults will have an injecting history – combining estimates of people currently on opioid substitution treatment and ex-injecting drug users [14, 15]. Third, early pilot studies suggest that it is likely that 80 or more people for an average practice will be identified by the algorithm. This gives approximately 1840 people per arm and substantial power to detect a difference in uptake of HCV testing. In addition, if we assume that two thirds of people diagnosed with chronic HCV attend hepatology for assessment then the case-finding rates of 5 and 17 % convert to HCV treatment readiness rates of 1.3 and 4.4 % and 72 % power (with an ICC of 0.05) to detect a true difference in HCV treatment readiness. As we will adjust the statistical analysis for testing rate and whether a practice is within or outside the Bristol area, this will accommodate some of the clustering, and so it is likely that we will have sufficient power to detect a difference in HCV treatment assessment as well as HCV testing uptake.

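### The stated model omits practice size, an allocation factor, and uses baseline testing only as a high/low flag, giving up some precision if either is prognostic

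*Protocol article*

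**What the plan says.** The randomisation paragraph under Study design stratifies practices by area (Bristol or not) and by testing rate, cut at 1% of the practice list. Allocation is also balanced on list size: "and minimised by practice size". On how common the high category is, it reports: "In 93 practices in our target area, 15 (16 %) had HCV high testing rates".

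The last paragraph of Secondary outcome measures sets the analysis for the primary outcome. The rate ratio "will be estimated in a negative binomial regression model", with two covariates: whether the practice is in Bristol, and "whether that practice has at baseline a high HCV testing rate or not". Practice size is not named. The same approach carries over to the secondary outcomes.

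The Sample size section gives 72% power for treatment readiness (1.3% against 4.4%, ICC 0.05, about 1840 patients per arm). It expects adjustment for testing rate and area to absorb part of the clustering and so make power for treatment assessment sufficient.

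**The concern.** Two features of the covariate list look less efficient than they need be.

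- **Practice size.** A factor is balanced by design and then left out of the model. If it predicts outcome, its variance stays in the error term and the reported standard error is larger than it need be.
- **Baseline testing.** A practice cannot be classed as above or below 1% without knowing its rate, so the numerical value should already be held. The model keeps only the flag, so all differences among the roughly 39 low-rate practices are discarded.

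Precision is what is at stake. It matters most for the later steps of the care pathway, where the Sample size section itself looks to covariate adjustment to improve on 72% power.

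**Working it through.** **The plan's own figures.** For 5% against 17% at 90% power and two-sided 5% (two-sidedness assumed), the continuity-corrected formula gives 158 per arm. Multiplying by the design effect 1 + 9 × 0.05 = 1.45 gives 229.1, that is 22.9 practices of 10. This agrees with "46 practices (23 intervention and 23 control, 230 high-risk patients identified in each arm". For treatment readiness, the design effect at 80 per practice is 1 + 79 × 0.05 = 4.95. The effective size is 1840 / 4.95 = 371.7 per arm, and power for 1.3% against 4.4% is 72.0%. Both figures reproduce.

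**How many practices carry the flag.** 46 × 15/93 = 7.4, assuming recruited practices resemble the 93.

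**What the flag retains.** Assume the baseline rate is roughly normal on some scale. With p = 15/93 = 0.161, the cut is at z = 0.989, where the normal density is 0.2446. The correlation between the rate and its flag is 0.2446 / √(0.161 × 0.839) = 0.665. Squared, this is 0.442, so the flag keeps about 44% of the linear information.

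**Effect on treatment-readiness power.** Let r be the correlation between the baseline rate and the practice-level outcome. The documents give no value, so a range is shown. The design effect after adjustment is 0.95 + 4.0 × (1 − f), where 4.0 = 80 × 0.05, f = r² for the continuous rate and f = 0.442 r² for the flag.

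| r | Design effect, flag | Design effect, continuous | Power, flag | Power, continuous | CI width, flag / continuous |
|---|---|---|---|---|---|
| 0 | 4.95 | 4.95 | 72.0% | 72.0% | 1.00 |
| 0.2 | 4.88 | 4.79 | 72.6% | 73.4% | 1.01 |
| 0.3 | 4.79 | 4.59 | 73.4% | 75.2% | 1.02 |
| 0.4 | 4.67 | 4.31 | 74.5% | 77.8% | 1.04 |
| 0.5 | 4.51 | 3.95 | 76% | 81% | 1.07 |
| 0.6 | 4.31 | 3.51 | 78% | 86% | 1.11 |

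CI width is the square root of the ratio of the two design effects. The calculation gives no credit to area, which is already in the model and may carry some of the same information.

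**Practice size.** Suppose size explains 10% of between-practice variance. In closed form, including it multiplies the standard error by √[(0.95 + 4.0 × 0.9) / 4.95] = √(4.55 / 4.95) = 0.959, about 4% smaller. Simulating the negative binomial model with 46 practices of 80 (250 runs) gave 1.6% smaller. The cost of leaving size out is therefore about 2–4% in that case, and about nil in simulation when size was not prognostic.

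**The primary outcome.** At 10 per practice, 230 / 1.45 = 158.6 per arm gives 93% power (formula without continuity correction). At 80 per practice, 371.7 per arm gives more than 99.9%, with no covariates at all.

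**The case against.** The strongest reply is that the flag is the stratification factor exactly as randomised, and analysing a stratified design on its own strata is standard. That stands: the flag is not an error, and a continuous term brings an assumption about functional form. A plain log rate would also be undefined for a practice with no baseline tests.

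A second reply concerns how well the baseline rate can predict. It counts tests against the whole practice list. The outcome is testing among patients picked out by an audit that excludes those tested in the previous year, and half the practices receive an intervention meant to change testing. Treatment readiness is further removed again, since it depends on attending hepatology. Correlations of 0.5 or 0.6 are therefore assumptions, and at 0.2 to 0.4 the gain is only about 1 to 3 power points. This also stands, and is why the low values are shown.

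Third, nothing says that size predicts the proportion tested; minimising on it may only even out patient numbers between arms. That is fair, and makes the size component conditional too. An offset for the number of high-risk patients, if used, would scale the expected count but would not adjust the testing rate for size.

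Finally, a separate analysis plan might add covariates. It might, but this article names its covariate list, and that list does not match its own allocation factors.

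A reader might infer that the effect estimate is biased, or that the primary comparison is short of power. Neither follows: leaving out a balanced covariate does not bias the comparison, and primary power is ample. A reader might also take the 44% to mean that more than half the power gain is always lost in any important sense. It is a share of explained variance, and when little is explained it amounts to a point or so of power.

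**Conclusion.** The point holds as a conditional efficiency improvement. The mismatch between allocation factors and covariates is plain on the page, and about 7 of 46 practices would carry the flag if recruits resemble the target area. The size of the loss depends on two quantities the documents do not give: how strongly the baseline rate, and how strongly practice size, predict practice-level outcome. For treatment readiness, replacing the flag by the continuous rate is worth under 1 power point at a correlation of 0.2, about 5 at 0.5 and about 8 at 0.6. If neither covariate is prognostic, nothing is lost. These figures rest on ICC 0.05, 80 patients per practice and an approximately normal baseline rate.

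The Sample size section is not contradicted. It claims only that adjustment for testing rate and area will absorb part of the clustering, and the model adjusts for both. But its expectation of sufficient power above 72% is where a better covariate could help.

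**What to change.** In the last paragraph of Secondary outcome measures, add practice list size (for example log list size) to the pre-specified covariates in all models. Add the continuous baseline testing rate, on a scale that allows zero, alongside or in place of the flag. Keep area, and report the model with the as-stratified flag as a sensitivity analysis.

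The cost is a sentence or two of text, one or two extra parameters with 46 practices, and an assumption about functional form. Both variables are needed for randomisation, so no new data collection should be required. The trial was still recruiting practices at submission, so the change could be fixed before outcomes are seen.
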